| **Statistical analysis** | **Estimation of sample sizes:**  This is a superior efficacy test study. The efficiency test was conducted on the main therapeutic effect index. Setting bilateral α = 0.05, *β* = 0.20, and the standard deviation SD = 7.8 mmHg, the difference of the antihypertensive effect in the two groups were detected as *D* = 3 mmHg. The distribution ratio of the patient cases in the two groups was 1:1. The estimated minimum sample size was 108 pairs. Taking into account of the factors such as dropping, the present research plan included 260 cases into the two groups with 130 cases of patients in the experiment group and the control group, respectively.  **Statistical analysis of the data set:**  Statistical analysis was conducted by using the full analysis set, per-protocol population set and safety data set. The quality control was strictly carried out in the whole process of the data statistics to ensure the authenticity of the assessment of data.  Full analysis set (Full analysis set, FAS): according to the fundamental principle of intention to treat (ITT), all the randomly enrolled subjects with more than one medication administration record and effective evaluation were included in the full analysis set. When selecting full analysis set for analysis, the latest observation LOCF (LOCF) estimation method was adopted for the estimation of the missing values. Full analysis set is the main effectiveness method for the evaluation of population in the present study.  The Per-Protocol set (PPS): PPS included all the subjects with completed prescribed treatment protocal or no serious violations of tests. The exact definition of the serious violations of the scheme will ultimately determined in the data auditing, which generally included the following situations (but they are not limited to these cases): Not meeting the inclusion criteria, having interference treatment after being selected, poor compliance, interview beyond the time window. PP set is a secondary analysis of the crowds of the effectiveness, but if the results were inconsistent with the full analysis set, detailed analysis should be done on the inconsistent results.  Safety data set (Safety Set, SS): the definition of safety data set was the subjects that at least received one time drug treatment.  **Statistical analysis method:**  Statistical analysis was conducted by using the SAS9.13 statistical analysis software for calculation. Quantitative description of the parameters included the calculation of mean, standard deviation, median, minimum value and maximum value. The description of the classified index employed the case number and percentage of the cases.  Descriptive statistics were conducted on the completion of the study. The comparison among groups was conducted on the demographic and baseline characteristics to analyze the equilibrium between groups.  Analysis of the main outcome measures: the main efficacy index will use the test of superiority. In addition, the dereasee value os DBP of each subject after treatment of 8 weeks will also be calculated, and descriptions in each group were done (mean, standard deviation, median, minimum, maximum). Comparisons between groups used analysis of variance considering center effect.  Analysis of the secondary outcome indicators: the center effect was not considered in principle. Comparisons between groups employed the variance analysis, chi-square test or nonparametric statistical method.  Analysis of the safety evaluation: parameters of safety evaluation included adverse events/ adverse drug reaction (ADR)/important adverse events or serious adverse events, physical examination and laboratory examination and a 12-lead electrocardiogram. Detailed description was conducted on the cases of adverse events during the test. The incidence rates of the adverse events between the two groups were summarized and compared. The indexes of laboratory examination were statistically described. The difference between two groups was compared when it was necessary. A detailed description of the laboratory indexes and normal cases before treatments was conducted.  This study did not conduct interim analysis. |

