# The expected duration of research, the number of research center and of the case number of planning

The present research program is planned to enroll subjects from May of 2009, and finish grouping in August of 2009, and statistical analysis and summary will be conducted in December of 2009.

Research will be carried out in 8 National Research center. The study designs 1 treatment group and 1 placebo group. One hundred and eight cases of patients in each group can be evaluated, so a total of 216 cases of patients are needed to be evaluated. Considering a shedding rate of 20%, a total of 260 qualified cases of subjects with hypertension are needed to be enrolled.

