## Subjects compliances

For the compliances of the medication orders, the drug use situation was calculated according to the recovery quantity of the distributed drugs combined with the diary cards of the subjects;

Actual dose of drug taken by subjects

Compliance＝

The dose of drug should be taken by the subjects

If the compliance of subject  80％, or  120％, indicating that the compliance is poor, not entering the per protocol set for analysis.

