## Definition and selection of analytic set

The full analysis set and statistical analysis conducted in accordance with the scheme set set and data security. The whole process of statistical data will be strict quality control to ensure the authenticity of the data, assessment.

Full analysis set (Full analysis set, FAS): according to the intention to treat (ITT) principle, the random into groups, and the subjects more than once medication administration record and to evaluate the effectiveness of the enrolled in the full analysis set. In the choice of full analysis set analysis, the missing value estimation, can adopt the LOCF (LOCF) estimation method. Full analysis set is the main evaluation of the effectiveness of the study population.

The project sets (Per-Protocol set PPS): with the scheme set includes all completed treatment provisions scheme or no serious violations of test subjects. The exact definition of serious violations of the scheme will ultimately determine the data audit, generally include the following situations (but are not limited to these cases): Do not meet the criteria, interference treatment in selected, poor compliance, and visit beyond the time window. PP set is a secondary analysis of the crowd's effectiveness, but the results such as the full analysis set is inconsistent, to the detailed analysis of the inconsistent results.

Safety data set (Safety Set, SS): the definition of safety data set for at least the subjects received a drug treatment.

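### The per-protocol set is defined with *or* where *and* is needed: it admits completers with serious violations and contradicts the protocol's own compliance rule

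*Protocol*

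**What the plan says.** The PPS is defined twice. The Protocol summary (statistical analysis of the data set) says "PPS included all the subjects with completed prescribed treatment protocal or no serious violations of tests". Section 11.2 (Definition and selection of analytic set) has the same construction: "with the scheme set includes all completed treatment provisions scheme or no serious violations of test subjects".

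The summary then gives examples of serious violations: "Not meeting the inclusion criteria, having interference treatment after being selected, poor compliance, interview beyond the time window". It leaves the final list open: "The exact definition of the serious violations of the scheme will ultimately determined in the data auditing". Section 10.6 places a blind review before database lock.

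Section 7.3 (Subjects compliances) has a separate rule. It sets limits at 80% and 120% (the comparison signs did not survive in the text available) and says of a patient outside them: "indicating that the compliance is poor, not entering the per protocol set for analysis".

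On the roles of the sets, the summary says "Full analysis set is the main effectiveness method for the evaluation of population in the present study". The PPS is secondary, with the instruction that "if the results were inconsistent with the full analysis set, detailed analysis should be done on the inconsistent results".

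**The concern.** The two PPS conditions are completing the treatment and having no serious violation. Joined by *or*, either one is enough, and only a patient who fails both is removed. Three things follow.

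- The list of violations has no effect on anyone who completes. A completer who was ineligible or took interfering treatment stays in.
- A poorly compliant completer is in the PPS under the summary and Section 11.2, and out of it under Section 7.3.
- A patient who leaves early without a serious violation can qualify. Withdrawal by choice, for an adverse event or on the blood-pressure criterion are all exit reasons in Section 4.3, and none is among the listed examples of violations. Last observation carried forward is stated only for the FAS.

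What is at stake is the use of the PPS. The plan compares it with the FAS and acts on any disagreement. A PPS that retains completers with violations is poorly placed to show whether those violations influenced the result.

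**Working it through.** **Step 1. Membership by patient type.** No figures are needed here.

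| Patient | Completed | Serious violation | Summary and 11.2 (*or*) | With *and* |
| --- | --- | --- | --- | --- |
| Completer, no violation | yes | no | in | in |
| Completer, ineligible, interfering treatment or out-of-window visit | yes | yes | in | out |
| Completer, poor compliance | yes | yes | in (Section 7.3: out) | out |
| Dropout, no violation | no | no | in | out |
| Dropout with violation | no | yes | out | out |

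The third row is a direct contradiction within the protocol. The second shows the violation list without effect for completers. Deferring the definition of a serious violation to the data audit does not help, because the audit can change who counts as a violator but not the connective.

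**Step 2. Size.** The protocol gives no planned PPS size, so there is no figure of its own to reproduce. Inputs:

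- N = 260 and a loss rate d = 20%, from Section 3: "Considering a shedding rate of 20%, a total of 260 qualified cases of subjects with hypertension are needed to be enrolled". Taken at face value, 0.20 × 260 = 52 non-completers.
- Serious-violation rate v: not in the protocol. Assumed at 2.5%, 10% and 20%.

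Formulas:

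- *or* removes patients who are both non-completers and violators: N × d × v if the two are independent, 0 if they never coincide, and N × min(d, v) if they overlap fully.
- *and* removes patients who are either: N × [1 − (1 − d)(1 − v)] if independent, with a range from N × max(d, v) to N × (d + v).

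| v (assumed) | *or*, independent | *or*, range | *and*, independent | *and*, range |
| --- | --- | --- | --- | --- |
| 2.5% | 260 × 0.20 × 0.025 = 1.3 (0.5%) | 0 to 6.5 | 260 × (1 − 0.80 × 0.975) = 57.2 (22%) | 52 to 58.5 |
| 10% | 260 × 0.20 × 0.10 = 5.2 (2%) | 0 to 26 | 260 × (1 − 0.80 × 0.90) = 72.8 (28%) | 52 to 78 |
| 20% | 260 × 0.20 × 0.20 = 10.4 (4%) | 0 to 52 | 260 × (1 − 0.80 × 0.80) = 93.6 (36%) | 52 to 104 |

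At every assumed rate and any overlap, *and* removes at least the 52 non-completers. What *or* removes runs from nobody to 52 (20%).

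**Step 3. How much overlap is plausible?** Some is certain in principle. Section 4.3 lists serious eligibility violations and poor compliance as reasons for exit, and a patient who leaves for either fails both conditions. If compliance is reckoned against all 56 days of double-blind treatment, 0.80 × 56 = 44.8, so a patient who stops before about day 45 is below 80% and also fails both. Section 7.3 divides by the dose that should have been taken and does not say whether that runs to day 56 or to the day of stopping. The overlap therefore cannot be fixed from the protocol.

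**The case against.** The strongest reply is that the intent is plain. A list of serious violations makes sense only if violators are removed, Section 7.3 says poor compliers are removed, and the English is visibly a rough translation. Completing the prescribed treatment may also mean having followed it rather than having reached week 8, in which case a poor complier has not completed and the conflict with Section 7.3 goes away. The PPS is secondary in any case.

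Much of this stands. *And* was probably meant, and the primary analysis is not touched. But the *or* appears in both places that define the set. The alternative reading of completion resolves only the compliance conflict: an ineligible patient who took every dose still enters, and so does a dropout without a violation.

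Stronger readings are tempting, and the documents do not support them.

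- A reader might infer that the PPS would be almost identical to the FAS, so that agreement is close to automatic. That needs a low violation rate or little overlap with dropout. Neither is given, and the range above runs to 20% removed.
- A reader might infer that dropouts in general stay in. Only those without a serious violation do.
- A reader might scale from the earlier phase II trial reported in Section 1.2, treating its 34 dropouts and 7 exclusions as separate patients who would all be retained under *or*. The counts do not reconcile with that: 34 + 7 = 41, while 283 − 246 = 37 were outside its PPS. The rule for that PPS is not reported either.

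There is also a fair objection to the remedy. *And* makes the PPS completers-only and removes patients who left under the protocol's own exit criteria without violating anything. Exits on blood pressure are related to the outcome and could differ between arms. That is a reason to keep the PPS secondary.

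**Conclusion.** The point holds as a defect in a stated rule. As written, the PPS admits completers with serious violations, can admit dropouts without one, and contradicts Section 7.3 for the poorly compliant completer if completion means reaching the end of treatment. The admission of other violators does not depend on that reading or on any assumed rate.

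The numerical effect is conditional. With 20% of 260 lost and violation rates assumed at 2.5% to 20%, independent of dropout, *or* removes 0.5% to 4% and *and* removes 22% to 36%. Without independence, *or* removes 0% to 20%. How close the PPS would come to the FAS cannot be said from the protocol.

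The consequence is a weaker consistency check in a secondary analysis. The superiority test on the FAS, its alpha and its power do not change. The rule should still be corrected, because it decides who is analysed and the correction is nearly free.

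**What to change.** In the Protocol summary and in Section 11.2, define the PPS as patients who completed the 8-week double-blind treatment *and* had no serious protocol violation, as fixed at the blind review before unblinding. Cross-refer to the existing compliance rule in Section 7.3 so that all three places give the same membership. No new threshold is needed.

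The drafting cost is one word in two places plus a cross-reference, handled as a protocol revision under Section 12.6. The analytic cost is a smaller, completers-only set: with 20% of 260 lost, at least 52 patients are removed, including those who left under the protocol's exit criteria. The PPS should therefore remain secondary to the FAS, and any difference between the two should be read with that selection in mind.

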
**Experimental flow chart**

|  | **Screening and cleaning periods** | | | **Baseline period** | **The treatment period (window period ± 3 days)** | | | **Safety observation period 5 (window period ± 7 days)** | | | |
| --- | --- | --- | --- | --- | --- | --- | --- | --- | --- | --- | --- |
| **Screenig** | | **Cleaning** |
| Interview times | **1** | | | **2** | **3** | **4** | **5** | **6-8** | **9** | **10-11** | **12** |
| Interview time (week) | **－3～－2** | **－2～0** | | **0** | **2** | **4** | **8** | **9-32** | **40** | **48-56** | **64** |
| Signing written informed consent | **X** |  | |  |  |  |  |  |  |  |  |
| Collecting Medical History | **X** |  | |  |  |  |  |  |  |  |  |
| Physical examination | **X** |  | |  |  |  | **X** | **X6** | **X** | **X6** | **X** |
| Blood pressure and heart rate in sitting position | **X** |  | | **X** | **X** | **X** | **X** | **X** | **X** | **X** | **X** |
| Auditing inclusion/exclusion criteria | **X** |  | | **X** |  |  |  |  |  |  |  |
| Urine pregnancy test 1 | **X** |  | |  |  |  | **X** |  |  |  | **X** |
| Routine blood test 2 | **X** |  | |  |  |  | **X** | **X6** | **X** | **X6** | **X** |
| Routine urine test 3 | **X** |  | |  |  | **X** | **X** | **X6** | **X** | **X6** | **X** |
| Liver function（ALT、AST、  TBil） | **X** |  | |  |  | **X** | **X** | **X6** | **X** | **X6** | **X** |
| Renal function（Bun、Cr、  Ua） | **X** |  | |  |  | **X** | **X** | **X6** | **X** | **X6** | **X** |
| Blood fat（TG、TC、HDL、LDL） | **X** |  | |  |  |  | **X** | **X6** | **X** | **X6** | **X** |
| Fasting blood-glucose（FPG） | **X** |  | |  |  |  | **X** | **X6** | **X** | **X6** | **X** |
| Blood electrolytes（K、Na、  Cl） | **X** |  | |  |  | **X** | **X** | **X6** | **X** | **X6** | **X** |
| 12 electrocardiograph（ECG） | **X** |  | |  |  |  | **X** |  | **X** |  | **X** |
| The drug release of the cleaning period 4 | **X** |  | |  |  |  |  |  |  |  |  |
| The drug recovery of the cleaning period |  |  | | **X**4 |  |  |  |  |  |  |  |
| 收Release and recovery of the research drugs |  |  | | **X** | **X** | **X** | **X** |  |  |  |  |
| Drug release and recovery of the safety observation period |  |  | |  |  |  | **X** | **X** | **X** | **X** | **X** |
| Release, recovery and transcription of diary cards of the subjects | **X** | **X** | | **X** | **X** | **X** | **X** |  |  |  |  |
| Recording concomitant medication | **X** | **X** | | **X** | **X** | **X** | **X** | **X** | **X** | **X** | **X** |
| Recording adverse events | **X** | **X** | | **X** | **X** | **X** | **X** | **X** | **X** | **X** | **X** |

1. It applies only to women of childbearing age.

2. Whole blood test indexes include the following aspects: total numbers of erythrocytes and leukocytes, and percentages of neutrophile granulocytes and lymphocytes, platelet count, hemoglobin and hematocrit.

3. The indexes of routine urine detection inlcude the following aspects: urine leukocytes, urine erythrocytes and urine proteins and carbohydrate.

4. The released drugs of the cleaning period can meet applciation for 17 days. The cleaning period was 14 days. The participants must be back to the hospital in 14 ± 3 days for baseline interview.

5. Interview was conducted once every 8 weeks, and a total of 7 interviews were carried out.

6. If there is abnormity of the laboratory examinations in the previous double-blind period, reexamination must be conducted. If it is normal in the previous results, the researchers can decide whether to inspect according to their own circumstances;

Note: according to the conditions of the patients, the researchers can increase the safety inspection of the subjects at any time.

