## Exclusion criteria

The subjects meeting one of the following conditions will not be selected in the test:

1. Having been diagnosed or suspected as secondary hypertension;

2. The difference of systolic blood pressure in seated place measured for three consecutive times is greater than 20 mmHg, and the difference of diastolic pressure is greater than 10 mmHg;

3. Sick sinus syndrome, II~III atrial ventricular block, atrial flutter, atrial fibrillation, or other malignant arrhythmia;

4. Aneurysm in conducting artery or dissecting aneurysm, percutaneous tranluminal coronary angioplasty (PTCA) or other cardiac surgery;

5. Unstable angina pectoris, acute myocardial infarction, cardiac failure, and cerebral accidents within recent 6 months;

6. Asthma or moderate to severe chronic obstructive lung disease;

7. Uncontrolled diabetes, FBG≥11mmol/L or with complications (degenerative nephritis and peripheral neuropathy);

8. Renal arterial stenosis;

9. Renal inadequacy ( Cr>1.5×ULN (the upper limit of the normal range);

10. Serious hepatopathy or hepatic inadequacy (ALT, AST or TBIL> 2×ULN);

11. Electrolyte disturbances (blood potassium or sodium abnormality);

12. Subjects with lower blood volume;

13. Female subjects with pregnancy or in lactation;

14. Subjects with drug or alcohol dependence;

15. Concomitant treatment with other drugs which will affect the blood pressure;

16. Subjects with resistant hypertension;

17. Allergy to any ingredient in the study;

18. attend other clinical trail within 3 month;

19. Suspected as white overcoat hypertension according to the judgment of investigators;

20. Subjects are thought unsuitable for the study by investigators.

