### Baseline period (Interview 2, 0 week)

After the subjects taking the placebo for 2 weeks, the following aspects should be conducted:

- - Rest sitting blood pressure and heart rate were measured: the measurement method is the same as that of the screening period;
  - Auditing the inclusion/exclusion criteria, the qualified subjects were distributed with random numbers according to the order of grouping from small to large order (i.e. drug number);
  - Distribution of drug of the first ~ the second week treatment period (including 3 days of alternate drug) according to the random numbers issued;
  - Recovery of the research drugs in the placebo washout period of 2 weeks;
  - Transfer and recording of diary cards of subjects;
  - Recording adverse events and concomitant treatments.

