### Finishing of the random therapy (Interview 5, 8 weeks ± 3 days)

After the subjects taking 8 weeks of the research drugs in the double-blind randomized treatment period, the following aspects are needed:

- - Physical examinations: physical examination of all body systems including weight;
  - Resting sitting blood pressure and heart rate were measured: the measurement method was as the same as that of the screening period;
  - Laboratory and auxiliary examinations: including urine pregnancy test (limited to women of childbearing age), whole blood test, urine routine test test, liver function, renal function, fasting blood glucose, blood lipid, blood electrolyte and 12-lead electrocardiogram.
  - Recovery of the fifth ~ eighth week remaining study drug and counting;
  - Distribution of Allisartan Isoproxil tablets for 9-weeks doses;
  - Recovery, transfer and recording of the diary cards of subjects;
  - Recording adverse events and concomitant treatments.

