### The safety observation period (Interview 6-11, 9-56 weeks, every interview for 8 weeks, the window period ± 7 days)

In order to observe the long-term efficacy and safety of the research drugs, all the subjects would participate in the safety observation period research of 56 weeks voluntarily after they finish the double-blind randomized study of 8 weeks, during which each subject will receive 240 mg Allisartan Isoproxil tablet treatment once a day, and the subjects should visit the doctor every 8 weeks:

- - Resting sitting blood pressure and heart rate were measured: the measurement method is the same as that of the screening period;
  - Laboratory examinations: urine routine test test, liver function, renal function and serum electrolyte (if the laboratory indicators are abnormal in the observation of former 8 weeks, please reexamine; if it is normal, please judge freely whether reexamination is necessary according to the circumstances);
  - Distribution of Allisartan Isoproxil tablets for 9 weeks doses;
  - Residual drug recovery of the past 8 weeks and counting;
  - Recovery, transfer and recording of the diary cards of the subjects;
  - Recording adverse events and concomitant treatments.

The interview 9, namely the interview of the subjects taking the research drugs for 32 weeks during the safety observation period, in addition to the above items, the following aspects are also needed to be conducted:

- - Physical examination: physical examination of all body systems including weight;
  - Laboratory examinations: urine routine test test, liver function, renal function and serum electrolyte;
  - Laboratory and auxiliary examinations including whole blood test, fasting blood glucose, blood lipid, blood electrolyte and a 12-lead electrocardiogram.

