### Measures of subjects after pregnancy

During the study period subjects after pregnancy, must immediately stop clinical trials and told the researchers. In the treatment of study within 3 months after the end of pregnancy must also report to researchers. Researchers should put all the pregnant women with pregnancy report report to Hangzhou Tigermed Co. Ltd. in 24 hours (CRO) and sponsor. Researchers should provide the consultation, discussion on the risk of pregnancy and its influence on the fetus. Continued monitoring of patients to the end of pregnancy. The final results should be pregnancy providing research sponsor.

To participate in the study subjects were pregnant wife should also report to the researchers and the sponsor. To provide consultation and follow-up of the pregnant wife of.

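### No pregnancy test is scheduled at randomisation or between weeks 8 and 64 on active drug, although the protocol excludes pregnancy and requires an immediate stop if it occurs

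*Protocol*

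**What the plan says.** The flow chart in the Protocol marks the row "Urine pregnancy test 1" (the 1 is a footnote limiting it to women of childbearing age) at Interviews 1, 5 and 12. The cells for Interviews 2, 3, 4 and 6 to 11 are blank. The visit lists in Sections 5.3.1 to 5.3.7 and the summary of timing in Section 9.1.2 give the same three occasions, so the schedule is consistent.

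Four other provisions bear on it:

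- **Exclusion.** Criterion 13 in Section 4.2 is "Female subjects with pregnancy or in lactation".
- **Randomisation visit.** Section 5.3.2 lists "Auditing the inclusion/exclusion criteria, the qualified subjects were distributed with random numbers" and the issue of the first double-blind drug, but no pregnancy test. On the interval since screening, the flow chart notes say "The participants must be back to the hospital in 14 ± 3 days for baseline interview".
- **Safety period.** Interview 5 includes the test and also "Distribution of Allisartan Isoproxil tablets for 9-weeks doses". Subjects who continue take 240 mg daily for 56 weeks with visits every 8 weeks. Section 5.3.6 sets out an enlarged examination at "The interview 9, namely the interview of the subjects taking the research drugs for 32 weeks during the safety observation period", which omits the pregnancy test.
- **Stop rule.** Section 9.3.4 says "During the study period subjects after pregnancy, must immediately stop clinical trials and told the researchers".

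**The concern.** The exclusion and the stop rule work only if pregnancy is detected, and the schedule leaves two intervals without a test.

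The first is at randomisation. Pregnancy status can change during the washout, and a conception shortly before screening may be too early to test positive. A woman in either position can pass the eligibility check at Interview 2 and be dosed, with no scheduled test until week 8.

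The second is the safety period. After Interview 5 no test is scheduled until the end of 56 weeks of treatment, during which every participating woman takes active drug. A pregnancy in that time is found only if she reports it, an investigator suspects it, or she leaves early and the exit test is done.

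At stake are the safety of women of childbearing age and the enforcement of the protocol's own rules. The primary endpoint, sample size and randomised comparison are untouched.

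**Working it through.** The plan states no figure to reproduce. The check compares the schedule with the visit lists and computes the intervals.

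**Inputs.** Screening is at week -3 to -2, before the placebo washout (Section 5.3.1). The washout return window is 14 ± 3 days (flow chart notes). Interview 5 is week 8 ± 3 days (Section 5.3.5). Interview 9 is week 40 ± 7 days and Interview 12 is week 64 ± 7 days (flow chart, Sections 5.3.6 and 5.3.7). Day 0 is Interview 2, taken as the day of the first double-blind dose.

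**Screening test to first dose**
- Nominal: 2 × 7 = 14 to 3 × 7 = 21 days.
- Within windows: shortest 14 − 3 = 11; longest 7 + (14 + 3) = 24 days.

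**First dose to next test**
- Nominal: 8 × 7 = 56 days; within the window 53 to 59.
- Screening test to week 8 test: 14 + 56 = 70 to 21 + 56 = 77 days nominal.

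**Week 8 test to week 64 test**
- Interview 5 is day 56 (53 to 59); Interview 12 is day 64 × 7 = 448 (441 to 455).
- Nominal gap: 448 − 56 = 392 days.
- Within windows: 441 − 59 = 382 to 455 − 53 = 402 days.
- Six visits fall inside it, at weeks 16, 24, 32, 40, 48 and 56.

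**Effect of adding tests in the safety period**

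| Schedule | Longest nominal gap | Longest gap within windows |
| --- | --- | --- |
| As written | 392 days | 402 days |
| Plus Interview 9 (day 280, 273 to 287) | 280 − 56 = 224 days | 287 − 53 = 234 days |
| Every 8-weekly visit | 56 days | 56 + 14 = 70 days |

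With Interview 9 added, the second interval is 448 − 280 = 168 days nominal (at most 455 − 273 = 182).

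**Other rows of the chart.** There are nine laboratory and ECG rows: pregnancy, blood, urine, liver, renal, lipids, glucose, electrolytes and ECG. Eight have a fixed mark at Interview 9. Pregnancy is the only one with no entry anywhere from Interview 6 to 11. The routine urine test does not fill the gap: the chart notes define it as leukocytes, erythrocytes, proteins and carbohydrate.

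**Other routes to detection.** These are self-report (Section 9.3.4), the chart's closing note that "the researchers can increase the safety inspection of the subjects at any time", the early-exit list in Section 5.3.8 (which includes the test, where feasible), and suspicion raised at an 8-weekly visit or the Interview 9 physical examination. None is a scheduled pregnancy test.

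**The case against.** The best reply is that the schedule contains no error or contradiction. Chart, visit lists and Section 9.1.2 agree, and the frequency of testing in the safety period is a matter of judgement on which the protocol sets no standard. That is right: this is a weak design choice, and no document standard selects Interview 9 over every visit.

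A second reply is that Interview 2 already requires the pregnancy exclusion to be checked again and that investigators may add tests. This also stands in part. The eligibility check exists; what is absent is a fixed test to support it. A strip at Interview 2 would still miss a very recent conception, so it narrows the risk without closing it.

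Third, the other laboratory-based exclusions (creatinine, liver enzymes and bilirubin, electrolytes, glucose) are also tested at screening and not repeated at Interview 2. True, but a pregnancy can begin within the washout and triggers an immediate stop.

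Fourth, the comparison with the other chart rows has limited force. Those rows monitor drug effects, seven of them are conditional at Interviews 6 to 8 and 10 to 11, and ECG is blank there. The comparison shows only that Interview 9 was built as a full fixed examination and this test was left out.

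Finally, the consequence cannot be sized and harm is not shown. The rat study in Section 1.2 gives 90 mg/kg/d as without toxic effect on dams or embryos, six times the rat pharmacodynamic dose, and calls 270 mg/kg/d slightly toxic. That study, as described, dosed gestation days 6 to 15 only. Section 9.3.4 also provides for 24-hour reporting, counselling and follow-up to outcome. What women are told at consent cannot be judged, because those pages are not at hand. All this limits the weight of the point, but it supplies no scheduled test in either interval.

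**Conclusion.** The point holds as a participant-safety weakness in a schedule that the protocol fixes itself. Randomised drug is issued on a pregnancy result nominally 14 to 21 days old (11 to 24 within windows), with the next test nominally 56 days later. In the safety period the interval between tests is 392 days (382 to 402).

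The case rests on the protocol's own exclusion and stop rules, not on demonstrated fetal harm. About half of those in the double-blind period take placebo under the 1:1 allocation, and the 56-week period covers only those who volunteer for it. The number of women of childbearing age is not stated, so no expected number of exposed pregnancies can be given. The change should be made. The Interview 2 test is the stronger half; how often to test in the safety period is more open to judgement.

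**What to change.** 1. Add the urine pregnancy test for women of childbearing age at Interview 2, to be read before the random number and drug are issued.
2. Add it in the safety period: at least at Interview 9 (week 40), preferably at each 8-weekly visit, since drug is dispensed there anyway.
3. Align the research steps in the Protocol summary, the flow chart, and Sections 5.3.2, 5.3.6 and 9.1.2.

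The cost is a strip and brief staff time at visits already planned, with no extra visit. A routine urine test is already fixed for everyone at Interview 9. A sample would be new at Interview 2, and is at present conditional at Interviews 6 to 8 and 10 to 11. A few women may be excluded at Interview 2, which the protocol already intends.
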